### Eligibility and Exclusion Criteria for Clusters (Workplaces) and Individual Participants

To be eligible for inclusion, workplaces must have a minimum of 8 employees and have accessible data on sickness absence (both self- and physician-certified) for the 2 years before allocation. Individual participants must speak Norwegian, be aged 18-70 years, and be employed ≥20% in the participating workplaces to be included in the trial. Workplaces that are experiencing profound reorganization (ie, >20% change in workplace staff during the research period) are excluded.

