### Timeline

Upon agreement to participate in the trial, all employees and management at the workplaces received the following by email from their employer: information about the trial, a PDF file with the individual informed consent form, and a link to questionnaire 1. Completed paper forms with individual informed consent were collected for 2 weeks, and then the random allocation was executed. Intervention periods were scheduled to be 12 months for both trial arms. Questionnaires 2 and 3 were to be completed 12 months and 24 months after allocation, respectively. Owing to the global pandemic, the trial was halted between mid-March 2020 and September 2020, and activities were reduced at several time points. Therefore, the intervention period and time points for questionnaires 2 and 3 were adjusted for workplaces included before April 2020 and in fall 2020, whereas workplaces included in 2021 were expected to follow the usual timeline. A flowchart of the study process is shown in Figure 1, and the timeline is shown in Figure 2.

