### Data Collection and Management

Trial questionnaires are electronic and administered by REDCap (Research Electronic Data Capture; Vanderbilt University) tools. Completed questionnaires are double-checked manually with informed consent forms to guarantee that only the data of those who have provided consent are used. Informed consent forms contain three sections to obtain separate consent for each of the following: use of questionnaire data, linkage to register data, and linkage to data from Tromsø 7, if applicable (Multimedia Appendix 1).

When answering questionnaire 1 at enrollment, participants registered their email address, to which links for later questionnaires will be mailed. Questionnaires 2 and 3 are completed at 12 and 24 months after allocation, respectively, or as appropriate owing to pandemic-related delays.

Questionnaires 1-3 all have the same questions on health-related quality of life, symptoms, work environment, and individual self-certified sickness absence. Validated questions were used when possible (see *Evaluation Outcomes* and Figure 2). Individual physician-certified sickness absence and health care use data are collected through register data for the period from 24 months before allocation to 24 months after allocation.

During the intervention period, workplaces report the time used for intervention activities on a quarterly basis. The sickness absence rate at the unit level is reported for the periods 24 months before allocation to allocation, the intervention period, and 12-24 months after allocation. Intervention staff registers the time spent on the preparation and execution of the intervention.

Workplaces that withdraw from the interventions before completing the intervention period are asked to continue to report their sickness absence data, and the individual participants are encouraged to answer all questionnaires, enabling intention-to-treat (ITT) analysis.

Data are stored on a secure research server at UNN with restricted access, which will also be used for data analysis. The personal national identification number will be used to collect register data according to consent. Data access is restricted to the project research group.

Study-specific personal identifiers will be used for all data storage, linkage, and analysis. The key list of identifiers is kept separate from the remaining data; access is restricted to PI NF and co-PI [name].

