#### Analysis of Data

Difference-in-difference analyses will be used to address any differences in sickness absence, health care refunds, and health-related quality of life between the trial arms at the unit level. Cost-effectiveness and cost-benefit analyses will compare the trial arms in terms of incremental costs based on direct and indirect costs related to interventions throughout the intervention period.

At the individual level, outcomes will be analyzed based on changes from enrollment. Moreover, 2-tailed *t* tests or Mann-Whitney *U* tests and chi-square tests will be used when appropriate. A generalized linear mixed effects Poisson model will be used to investigate possible differences in percentage of sick leave between the 2 trial arms. A multivariable, multilevel logistic, ordered logistic, and linear regression allowing for clustering at the unit level will be used according to the outcome measure (OM) analyzed. To consider changes owing to the pandemic-related temporary halt of the study, other statistical methods such as stratification will be relevant.

We will use 2-sided *P* values with *α*<.05 level of significance for all tests.

The analysis will be according to ITT regardless of protocol adherence.

Results will be reported in line with CONSORT (Consolidated Standards of Reporting Trials) guidelines.

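### The 20% staff-change exclusion is not limited to what is known before allocation; read literally, it would drop randomized workplaces and conflict with the intention-to-treat rule

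*Protocol article*

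**What the plan says.** The Protocol article, under Eligibility and Exclusion Criteria for Clusters, states: "Workplaces that are experiencing profound reorganization (ie, >20% change in workplace staff during the research period) are excluded". The same section sets a minimum size: "workplaces must have a minimum of 8 employees". The term for the window, the research period, is not defined anywhere in the article.

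The Timeline section gives the order of events: "Completed paper forms with individual informed consent were collected for 2 weeks, and then the random allocation was executed", and then "Intervention periods were scheduled to be 12 months for both trial arms". Data Collection and Management sets the length of follow-up, with individual absence and health care use taken from "register data for the period from 24 months before allocation to 24 months after allocation".

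On the analysis population, Analysis of Data states: "The analysis will be according to ITT regardless of protocol adherence". Data Collection and Management supports this: workplaces that withdraw "are asked to continue to report their sickness absence data, and the individual participants are encouraged to answer all questionnaires", and the stated purpose is to make an intention-to-treat analysis possible.

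**The concern.** Most of the window in which outcomes are observed lies after allocation. If the 20% threshold is counted over that window, an allocated workplace that crosses it is excluded under the eligibility section and retained under the analysis section. The article does not say which section prevails.

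This matters because staff change is not obviously independent of arm. Both interventions address work environment and work inclusion, and Evaluation Outcomes lists sustainable job participation among the programs' aims. Staff leaving or being replaced could therefore respond to the intervention and be related to sickness absence. That link is an inference; the article does not name turnover as an outcome. Removing a whole workplace removes it from all outcomes, at unit and individual level. Because arms are not blinded after allocation, the decision that a workplace has crossed an undefined threshold would also be made with the arm known.

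**Working it through.** The plan gives no figure for expected staff change, so there is nothing of its own to reproduce on this point. The check has three parts.

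**1. The sections side by side.**
- Eligibility: exclusion is defined by staff change over the research period.
- Timeline and Data Collection: allocation comes after a 2-week consent window; the intervention then lasts 12 months and data run to 24 months.
- Analysis of Data: intention to treat regardless of adherence.

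A workplace with a reorganization already under way or announced can be identified before the envelope is opened. A workplace whose staff changes unexpectedly in the following 24 months cannot. The eligibility sentence does not separate the two.

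**2. How easily the threshold is crossed.** Inputs from the article: threshold above 20%; minimum size 8; planning mean of 20 employees (Power Calculation). A middle size of 14 is added for illustration; it is close to consents per workplace, 1383/97 = 14.3, which is not a count of employees. Assumption: each worker leaves independently at annual rate a, every leaver counts as a change, and the window is the 24 months after allocation.

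Cumulative leaving: p = 1 - (1 - a)^2. Smallest number of changes above 20%: 2 of 8 (25%), 3 of 14 (21%), 5 of 20 (25%). Chance of crossing: P(Binomial(N, p) > 0.2N).

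| Annual rate a | p over 24 months | N = 8 | N = 14 | N = 20 |
|---|---|---|---|---|
| 5% | 1 - 0.95^2 = 0.0975 | 18% | 15% | 4% |
| 10% | 1 - 0.90^2 = 0.19 | 47% | 51% | 33% |
| 15% | 1 - 0.85^2 = 0.2775 | 70% | 79% | 69% |

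If only the 12-month intervention period is counted, a = 10% gives 19%, 16% and 4%. At a = 3% over 24 months the figures are 8%, 5% and 0.5%.

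**3. What exclusion could do to OM 1.** The Power Calculation targets a fall from 6.6% to 5.9%, which is 0.7 points, with SD 2.5. Let q be the share of workplaces excluded in an arm, and d the change in absence in excluded minus retained workplaces, in points. The retained mean is the full mean minus q x d. With no true effect, the bias in the HIW minus IWM difference is -(q_HIW x d_HIW - q_IWM x d_IWM). The values of q and d are assumptions.

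- 10% and 10% excluded, d = 2.5 in both arms: -(0.25 - 0.25) = 0.
- 5% and 15%, d = 1.25: -(0.0625 - 0.1875) = 0.125 points, 18% of 0.7.
- 5% and 15%, d = 2.5: -(0.125 - 0.375) = 0.25 points, 36% of 0.7.
- 10% and 10%, d = 1.25 (HIW) and 2.5 (IWM): -(0.125 - 0.25) = 0.125 points, 18% of 0.7.

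The sign reverses if the pattern between arms reverses. Loss of precision is a smaller matter: in a plain two-sample comparison of means with 45 and 52 workplaces, power for 0.7 points is 27.9%, falling to 25.6% if 10% are excluded from each arm and to 23.3% if 20% are.

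**The case against.** The best counter-argument is that this is an entry criterion, loosely worded. It stands under an eligibility heading beside criteria that are fixed at entry, and its main clause is in the present tense. Ongoing or planned reorganization could be raised at the introductory meeting with employers and union representatives. The Results section reports that 49 of 146 recruited workplaces (146 - 97) retracted before inclusion, with organizational challenges among the reasons. It then reports 97 allocated workplaces, 45 and 52, and no later removal. No section describes monitoring staff change after allocation or an analysis set without such workplaces. On that reading the eligibility and analysis sections agree.

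Much of this stands. It shows that a screening rule may be what was meant, and that harm has not been shown. It does not settle the text: the operational definition is tied to the research period, no sentence limits it to what is known before allocation, and the reported retractions were the workplaces' own decisions, not applications of this criterion.

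Three stronger readings are tempting and should not be drawn.
- A reader might infer that staff change in the window can be known only after allocation. Announced or ongoing reorganization can be known earlier.
- A reader might infer that the trial's results will be biased. Bias requires exclusion to be related to arm and to outcome change.
- A reader might infer that a third or more of the workplaces would be lost. That follows only from assumed turnover of at least 10% per year over 24 months, with each ordinary leaver counted. The criterion speaks of profound reorganization, which may mean something narrower, and the documents give no turnover rate.

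**Conclusion.** The point holds as an unresolved conflict in the text. The eligibility sentence, read literally, extends past allocation and would remove randomized workplaces; the analysis section would keep them; the article does not say which applies. It does not show that any workplace has been removed after allocation.

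The size cannot be fixed from the documents. Under independent leaving over 24 months, the chance that a workplace of 8 to 20 staff crosses the threshold is about 4-18% at 5% per year, 33-51% at 10% and 69-79% at 15%. Two changes suffice at the minimum size. The effect on OM 1 ranges from zero to 0.25 points in the scenarios shown, against a 0.7-point target, and rests entirely on the assumed exclusion shares and differences. The sections should be reconciled before the analysis because the rule is cheap to fix, and leaving it open allows unblinded exclusions.

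**What to change.** State that the criterion covers only reorganization known or announced before the allocation envelope is opened. State that all 97 allocated workplaces stay in the primary intention-to-treat analysis. Use staff change above 20% after allocation only to define a labelled sensitivity analysis, and report how often it occurred in each arm. If the sponsor does intend removal after allocation, the primary analysis should not be called intention to treat, and the exclusions must be reported by arm.

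Inclusion closed in July 2021, so the change now acts on the analysis rule. According to the article, no participant had received questionnaire 3 by February 20, 2022, and results were expected from autumn 2023, so the rule could still be set in advance at that date.

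The cost is one clarifying sentence and one extra analysis, plus a record of staff numbers after allocation. The downside is that workplaces that reorganized after allocation stay in the primary analysis and add some noise to it.

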### Interventions

#### HIW Intervention

Personnel from the NWCs and specialist health services work in collaboration to provide HIW interventions according to a standardized protocol. An initial meeting is held to define the workplace’s goals and plan the course of the intervention, followed by three 1.5-hour sessions over a 12-month period. During these sessions, health personnel present structured health information about musculoskeletal, pain, and mental disorders, and NAV personnel put this information in the context of work and the specific workplace. Between sessions, group-based workplace process exercises are carried out. During these exercises, challenges related to session content as well as topics around the work environment and work inclusion should be addressed.

In more detail, the first session aims to use health information on common neck and back complaints to increase workers’ ability to cope with them as individuals and collectively. It also presents tasks that foster reflection and dialogue on factors that promote the health and inclusion of workers with musculoskeletal complaints in the workplace. The second session aims to communicate health information regarding pain to increase workers’ ability to cope with it individually and collectively. The third session is similar to the first but with content related to common mental health complaints.

Both the sessions and the group exercises between the sessions should involve all workplace staff (management and employees). The group exercises should be active meetings that take place without the involvement of intervention personnel. Finally, at the end of the 3 sessions, an evaluation meeting is held to discuss possible further follow-up.

#### IWM Intervention (Treatment as Usual)

IWM consists of conventional welfare interventions given over a 12-month period by NWC personnel only. The interventions focus mainly on work inclusion and psychosocial work environment. There are several types of interventions available, some of which are presented in Figure 1. The choice of delivery is customized to the individual workplace; thus, treatment as usual varies according to the workplace’s demands. An evaluation meeting discussing possible further follow-up is optional.

A flowchart of intervention content and the study process is shown in Figure 1.

**Figure 1 figure1:**
[figure not shown]
Schematic overview of activities in the *Health in work* (HIW) and *inclusive work measure* (treatment as usual) interventions. IWM: inclusive work measure; NAV: Norwegian Labour and Welfare Administration.

### Intervention Personnel

Health personnel comprise employees from specialist health services from the University Hospital of North Norway (UNN), Finnmark Hospital in Kirkenes, or the Rehabilitation Center Finnmark in Alta. They work in the field of rehabilitation medicine; for example, as physiotherapists, medical doctors, or occupational therapists. NAV personnel are from NWCs located at multiple sites in the county of Troms and Finnmark. They are experienced in Inclusive Work Agreement processes and have different backgrounds (eg, teaching, management, human resources, and nursing). Many have previously delivered *atWork Troms* interventions. NWC personnel deliver both HIW and IWM interventions according to their portfolio. All intervention personnel undergo in-house training according to protocol, including observation of experienced personnel, literature, and courses.

### Adherence to the Trial Protocol and Concomitant Activities

Participating NWC personnel, health personnel, and workplaces are to register and report on activity and time spent on either HIW or IWM each quarter. The research team sends reminders about these reports as a means of improving adherence.

Participating workplaces in both groups are allowed to implement other workplace measures (eg, measures from occupational health services or from NAV). The pragmatic design does not restrict the type or number of other workplace measures except for the HIW intervention, which is exclusively reserved for the HIW group. The content and extent of the applied measures have to be reported to the research group. Individual employees have no study-specific restrictions.

### Recruitment

The main role of NWCs is to support workplaces that wish to address the development and maintenance of a good work environment independent of their level of sickness absence. Workplaces can contact NWCs, but NWCs also reach out to workplaces. NWC personnel have good knowledge of and contact with workplaces in the region. Through this contact, workplaces from the county of Troms and Finnmark were recruited for the trial. They were informed about the ongoing trial and the fact that they may be allocated to either the HIW or IWM intervention in an introductory meeting with employers and union representatives. After initial slow recruitment, an additional meeting with detailed information solely on the trial and its implications given by one of the research group members (mainly [name], occasionally NF or [name]) was added to increase participation.

### Timeline

Upon agreement to participate in the trial, all employees and management at the workplaces received the following by email from their employer: information about the trial, a PDF file with the individual informed consent form, and a link to questionnaire 1. Completed paper forms with individual informed consent were collected for 2 weeks, and then the random allocation was executed. Intervention periods were scheduled to be 12 months for both trial arms. Questionnaires 2 and 3 were to be completed 12 months and 24 months after allocation, respectively. Owing to the global pandemic, the trial was halted between mid-March 2020 and September 2020, and activities were reduced at several time points. Therefore, the intervention period and time points for questionnaires 2 and 3 were adjusted for workplaces included before April 2020 and in fall 2020, whereas workplaces included in 2021 were expected to follow the usual timeline. A flowchart of the study process is shown in Figure 1, and the timeline is shown in Figure 2.

**Figure 2 figure2:**
[figure not shown]
Timeline for enrollment, intervention, and assessment. GJS: Global Job Satisfaction; HIW: *Health in work*; IWM: inclusive work measure; KUHR: Norway Control and Payment of Health Reimbursement; NDSS–16: Nondirective and Directive Support Survey; NPR: Norwegian Patient Register; SHC: subjective health complaints; SWLS: Satisfaction With Life Scale.

### Assignment of Intervention

The randomization sequence was created using a computer-generated random number list [25] with a 1:1 allocation using random block sizes of 16 to 20. On the basis of this allocation, a sheet of paper was marked with either *HELSEIARBEID* (HIW) or *KTRIAARBEID* (IWM). The paper was then folded and placed in a sequentially numbered opaque envelope, and the envelope was sealed (allocation envelope). In this manner, a total of 104 allocation envelopes were produced. In November 2020, owing to an unexpectedly high number of retractions after initial recruitment but before inclusion in the trial, another 50 allocation envelopes were produced. Sequence generation and allocation concealment were performed independently by co–principal investigator (PI) [name], who was not involved in the recruitment or allocation of workplaces. A list of the envelope numbers and the intervention they contained was locked away in a file cabinet at UNN, to which none of the personnel (research, NAV, or HIW personnel) has access. The workplaces were consecutively numbered as they agreed to participate in the trial during recruitment. Final inclusion was not completed until informed consent forms were received from the respective workplaces. The corresponding numbered allocation envelope was then opened by the PI, NF, together with a research assistant. The workplace was notified of the intervention to which it had been allocated, as was the supervisor of the relevant NWC. The workplace identifier was noted on the allocation envelope and locked away in a file cabinet. Blinding beyond allocation was not relevant for obvious reasons.

### Data Collection and Management

Trial questionnaires are electronic and administered by REDCap (Research Electronic Data Capture; Vanderbilt University) tools. Completed questionnaires are double-checked manually with informed consent forms to guarantee that only the data of those who have provided consent are used. Informed consent forms contain three sections to obtain separate consent for each of the following: use of questionnaire data, linkage to register data, and linkage to data from Tromsø 7, if applicable (Multimedia Appendix 1).

When answering questionnaire 1 at enrollment, participants registered their email address, to which links for later questionnaires will be mailed. Questionnaires 2 and 3 are completed at 12 and 24 months after allocation, respectively, or as appropriate owing to pandemic-related delays.

Questionnaires 1-3 all have the same questions on health-related quality of life, symptoms, work environment, and individual self-certified sickness absence. Validated questions were used when possible (see *Evaluation Outcomes* and Figure 2). Individual physician-certified sickness absence and health care use data are collected through register data for the period from 24 months before allocation to 24 months after allocation.

During the intervention period, workplaces report the time used for intervention activities on a quarterly basis. The sickness absence rate at the unit level is reported for the periods 24 months before allocation to allocation, the intervention period, and 12-24 months after allocation. Intervention staff registers the time spent on the preparation and execution of the intervention.

Workplaces that withdraw from the interventions before completing the intervention period are asked to continue to report their sickness absence data, and the individual participants are encouraged to answer all questionnaires, enabling intention-to-treat (ITT) analysis.

Data are stored on a secure research server at UNN with restricted access, which will also be used for data analysis. The personal national identification number will be used to collect register data according to consent. Data access is restricted to the project research group.

Study-specific personal identifiers will be used for all data storage, linkage, and analysis. The key list of identifiers is kept separate from the remaining data; access is restricted to PI NF and co-PI [name].

